#### Feasibility outcomes

The following quantitative measures will be used [63]:
Intervention appropriateness measure (IAM)Acceptability of the intervention measure (AIM)Feasibility of the intervention measure (FIM)

Evaluation of participants’ perspectives of the intervention will be assessed via focus groups and/or semi-structured interviews using the following themes:
Experience of using the under-desk pedal machines, including factors perceived as affecting the pedal machine, issues (e.g. contextual, practical, individual, or others), and adverse consequences (e.g. work, health, or otherwise related)Experiences of the mHealth intervention components (e.g. Garmin watch)Organisational-level and management perspectives on using the pedal machineAcceptability of the overall intervention by the users, from a management and employee perspective

#### Progression criteria

As pilot studies are usually too small to estimate parameters required for estimating a sample size for a main cluster randomised trial (e.g. the intra-cluster correlation coefficient) with sufficient precision, and too small to provide reliable estimates of rates for process measures such as recruitment or follow-up rates, these are not calculated in the present study [86]. This study is an exploratory study and progression criteria should not be judged as strict thresholds but as guidelines using, for example, a traffic light system with varying levels of acceptability [86, 87]. We will decide whether or not to proceed to a fully powered RCT using the following assessment principles and progression criteria:
Green: indicates that we have met a criterion or we are within 10% of our stated progression targetsAmber: indicates that we are within 20% of our stated progression target, in which case we will critically review reasons for this and assess whether major changes to study methods are likely to realise significant improvementsRed: indicates that we are more than 20% from our target, in which case we will not, in the absence of clear extenuating circumstances, consider progression to a full trial

Progression criteria include protocol non-adherence and outcome data.

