##### Protocol adherence criterion

Green—≥ 80% of participants engage in > 60% of their cycling goal

Amber—60–79% of participants engage in > 60% of their cycling goal

Red—<60% of participants engage in > 60% of their cycling goal

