##### Retention progression criterion

Green—≥ 80% of participants provide main trial-related outcomes (SB/PA) at T2

Amber—60–79% of participants provide main trial-related outcomes at T2

Red—< 60% of participants provide main trial-related outcomes at T2

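### The general traffic-light rule and the numeric progression bands put the Green cut-off in different places, and no single target makes them agree

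*Protocol article*

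**What the plan says.** The Progression criteria section of the protocol article gives a general rule. Green means that "we have met a criterion or we are within 10% of our stated progression" target. Amber means within 20% of target, and leads to a critical review of the reasons and an assessment of whether major changes to methods would help. Red means more than 20% from target, and progression is then not considered unless there are clear extenuating circumstances. The same section says that the decision on a fully powered trial will use both these principles and the criteria that follow. It also says that the criteria are guidance and not hard cut-offs.

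Two criteria follow, each with its own numeric bands:

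- Protocol adherence: the top band is "Green—≥ 80% of participants engage in > 60% of their cycling goal". A share from 60% up to 79% is Amber, and anything lower is Red.
- Retention: the cut-offs are the same. The middle band is "Amber—60–79% of participants provide main trial-related outcomes at T2", with Green above it and Red for any share under 60%.

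The general rule refers to stated targets, but none is given apart from these bands. The article does not say whether 10% and 20% are percentage points or fractions of the target, or which of the two schemes governs if they disagree.

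**The concern.** The bands read as though they apply the general rule, but they place Green differently. The rule lets a result fall somewhat short of target and still be Green. The bands start Green at 80% and make everything from 60% to 79% Amber.

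Testing whether a future trial is viable is the first aim of the pilot, and these colours are the quantitative part of that judgement. The colours also carry different consequences: Amber brings a critical review, and Red a presumption against progression. With two schemes in force and no order between them, a result in the disputed range could be reported under either colour once it is known.

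**Working it through.** **Inputs**

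- General rule: Green met or within 10% of target, Amber within 20%, Red beyond 20% (Progression criteria).
- Bands: Green 80% or more, Amber 60–79%, Red below 60% (Protocol adherence criterion; Retention progression criterion).
- Planned number: 30 (Sample size). All 30 are taken as the denominator.
- Target T: not stated. T = 80% is assumed because the Green threshold is the only candidate figure. Other values are checked in steps 1 and 3.

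**Step 1. Can any target reproduce the bands?**

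| Reading | Green cut-off | Red cut-off | Distance between them |
|---|---|---|---|
| Rule, percentage points | T − 10 | T − 20 | 10 points |
| Rule, relative | 0.9 T | 0.8 T | 0.1 T, at most 10 points |
| Bands | 80 | 60 | 20 points |

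Matching both band cut-offs would require:

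- in points, T = 80 + 10 = 90% for Green and T = 60 + 20 = 80% for Red;
- in relative terms, T = 80/0.9 = 88.9% for Green and T = 60/0.8 = 75% for Red.

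No single target meets both conditions under either reading, so the mismatch does not depend on assuming 80%.

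**Step 2. Size of the conflict at T = 80%**

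- Points: Green from 70%, Red below 60%.
- Relative: Green from 0.9 × 80 = 72%, Red below 0.8 × 80 = 64%.

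| Count of 30 | Percent | Bands | Rule, points | Rule, relative |
|---|---|---|---|---|
| 17 | 56.7 | Red | Red | Red |
| 18 | 60.0 | Amber | Amber | **Red** |
| 19 | 63.3 | Amber | Amber | **Red** |
| 20 | 66.7 | Amber | Amber | Amber |
| 21 | 70.0 | Amber | **Green** | Amber |
| 22 | 73.3 | Amber | **Green** | **Green** |
| 23 | 76.7 | Amber | **Green** | **Green** |
| 24 | 80.0 | Green | Green | Green |

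Bold marks disagreement with the bands. In points the conflict is 21–23 of 30, Green against Amber, and Red agrees at 60%. On the relative reading it is 22–23 of 30, Green against Amber, and also 18–19 of 30, Red against Amber.

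**Step 3. Other targets**

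With T = 90% in points, Green agrees at 80%, but Red begins below 70%, so 18–20 of 30 is Red under the rule and Amber under the bands. With T = 75% on the relative reading, Red agrees at 0.8 × 75 = 60%, but Green begins at 67.5%, so 21–23 of 30 is again disputed. In a search of T from 50% to 100% in steps of 0.1%, at least 3 of the 31 possible counts changed colour under either reading.

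**Step 4. How likely is a disputed result?**

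Binomial probabilities with n = 30, treating participants as independent (an approximation, since they come from two worksites):

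| True rate | Chance of 21–23 of 30 | Chance of 22–23 of 30 |
|---|---|---|
| 70% | 43% | 27% |
| 75% | 46% | 33% |
| 80% | 33% | 26% |

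The disputed range is where a moderately successful pilot would often land.

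**The case against.** The strongest defence is that the article treats the criteria as guidance, and its account of the intervention development process is critical of relying on binary progression thresholds and favours qualitative, contextual assessment. The colours therefore do not settle progression mechanically. This stands, and it lowers the severity. It does not remove the mismatch: guidance allows judgement around a cut-off but does not say which of two cut-offs is meant.

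A second defence is that specific bands ordinarily prevail over a general principle, and that in points at 80% the bands match the rule except for the 10% allowance in Green (80 − 20 = 60). That is a plausible reading order. However, the article puts both schemes into use and states no precedence.

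A reader might infer more than the documents support:

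- *That the conflict is between going ahead and stopping.* In points at an 80% target, Red is below 60% under both schemes. A Red conflict needs the relative reading at that target, or an unstated target other than 80%. Nor is Red an absolute stop, since extenuating circumstances are allowed for, and the section attaches no instruction to proceed to Green.
- *That the colour will be picked after the event.* The bands are pre-specified, so this is a risk left open and not something the plan provides for.
- *That results between 79% and 80% have no colour.* No count out of 30 falls there. With 29 evaluable, 23/29 = 79.3% rounds to 79%, which is Amber. This is a rounding matter only.

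**Conclusion.** The point holds as an internal contradiction over where Green begins. That the two schemes cannot be reconciled follows from their spacing alone and needs no assumption about the target. The particular counts in dispute, 21–23 of 30 in points or 22–23 of 30 in relative terms, rest on an assumed target of 80% and a denominator of 30. The further Amber/Red conflict at 18–19 of 30 rests on the relative reading as well. Because the criteria are guidance and sit beside qualitative evidence, this is something that should be fixed and not a defect that undermines the pilot.

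**What to change.** Keep one set of cut-offs, settled before outcome data are seen. The simplest route is to let the explicit adherence and retention bands define the colours, remove the within-10% and within-20% definitions from the Progression criteria section, and leave its consequences for Amber and Red as they are.

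Alternatively, the authors could state the target, say whether the percentages are points or relative, and revise the bands to match. The article does not show which scheme was intended, so the choice is theirs.

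As a minor wording point, write Amber as at least 60% and below 80%.

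The change is to wording only and needs no new data, participants or procedures. If the explicit bands are kept, the cost is that a result of about 70–79% can no longer be called Green.

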##### Protocol adherence criterion

Green—≥ 80% of participants engage in > 60% of their cycling goal

Amber—60–79% of participants engage in > 60% of their cycling goal

Red—<60% of participants engage in > 60% of their cycling goal

##### Retention progression criterion

Green—≥ 80% of participants provide main trial-related outcomes (SB/PA) at T2

Amber—60–79% of participants provide main trial-related outcomes at T2

Red—< 60% of participants provide main trial-related outcomes at T2

### Data analysis

Descriptive analysis will account for the recruitment and retention. Quantitative analyses will be carried out using Statistical Package for the Social Sciences V.25 (IBM Corp., Armonk, New York, USA). Descriptive statistics (e.g. daily mean SB and PA in minutes, SD) will be provided for all questionnaire data, from the EMA information, and overall SB and PA as derived from the objective measure.

Participant experience of acceptability and satisfaction with the intervention, as well as trial-related processes, will be assessed using analysis of the focus groups and semi-structured interviews. Transcriptions of audio-recorded interviews will be analysed using thematic analysis [88]. At each stage, findings will be verified and discussed in order to assess the accuracy of the interpretation, promote reliability, and ensure rigour [89]. The main analysis of this study will include thematic analysis, and no software package will be used to analyse the data.

## Discussion

This paper describes the design of a cluster randomised wait-list crossover pilot feasibility trial that will test pilot outcomes which will ascertain if a future larger-scale RCT is viable. Acceptability and feasibility outcomes of this theory-led multicomponent intervention to reduce SB in professional males will also be discussed. The design builds on previous developmental work in the participating worksites. The current study, to our knowledge, will be the first study to target professional males using an intervention that combines an under-desk pedal machine; the utilisation of mHealth to target specific BCTs such as self-monitoring, social comparison, and goal-setting; and recruitment management staff to the study. This unique combination of components aims to reduce SB and increase LPA during participants’ working day. The design of the study has been underpinned by the socio-ecological theory acknowledging that an understanding and subsequent targeting of the intrapersonal, interpersonal, physical environmental, and cultural-level factors are likely to be required to achieve the greatest changes in behaviour [38].

Office workers are one of the largest occupational groups in high-income countries and are sedentary for a large proportion of their day; therefore, reducing their SB could have important public health implications by reducing this risk factor associated with chronic disease and mortality [15]. Reallocating just 30 min of SB, sleep time, or standing time with LPA has been found to beneficially affect body composition, including BMI and fat mass [31]; therefore, restructuring the physical environment to enable LPA is an important strategy.

The current randomised pilot feasibility study is designed to inform subsequent refinement of intervention content, in terms of acceptability and feasibility of the intervention components and measures, so that the format may be suitable for real-world implementation and evaluation in a future definitive trial. Its primary purpose is to address key design uncertainties, including the feasibility of recruiting eligible participants, as well as the appropriateness, acceptability, and feasibility of the intervention. The qualitative component of the study will allow for exploration of any issues surrounding the acceptability of the under-desk pedal machines, as well as the mHealth component from the perspectives of the users, which will include employees and management. It will also allow for exploration of the study procedures and assessment methods.

By assessing the potential effectiveness outcomes of SB and PA, and work engagement, and the perceived benefits of reducing workplace SB, the current pilot feasibility study will clarify the design of a future larger trial that will extend the current knowledge regarding the effectiveness of this type of multicomponent intervention to reduce occupational SB.

## Data Availability

Not applicable—protocol paper.

## Abbreviations

SB: Sedentary behaviour
METs: Metabolic equivalents
EE: Energy expenditure
PA: Physical activity
MPA: Moderate physical activity
WHO: World Health Organization
LPA: Light physical activity
BMI: Body mass index
SCT: Social cognitive theory
BCT: Behaviour change technique
MRC: Medical Research Council
rPARQ: Physical Activity Readiness Questionnaire
EMA: Ecological Momentary Assessment
UWES-9: Utrecht Work Engagement Scale
IAM: Intervention appropriateness measurement
AIM: Acceptability of intervention measurement
FIM: Feasibility of intervention measurement
